## Abstract

**Background:**

Household air pollution exposure is a major health risk, but validated interventions remain elusive.

**Methods/Design:**

The Ghana Randomized Air Pollution and Health Study (GRAPHS) is a cluster-randomized trial that evaluates the efficacy of clean fuels (liquefied petroleum gas, or LPG) and efficient biomass cookstoves in the Brong-Ahafo region of central Ghana. We recruit pregnant women into LPG, efficient cookstove, and control arms and track birth weight and physician-assessed severe pneumonia incidence in the first year of life. A woman is eligible to participate if she is in the first or second trimester of pregnancy and carrying a live singleton fetus, if she is the primary cook, and if she does not smoke. We hypothesize that babies born to intervention mothers will weigh more and will have fewer cases of physician-assessed severe pneumonia in the first year of life. Additionally, an extensive personal air pollution exposure monitoring effort opens the way for exposure-response analyses, which we will present alongside intention-to-treat analyses. Major funding was provided by the National Institute of Environmental Health Sciences, The Thrasher Research Fund, and the Global Alliance for Clean Cookstoves.

**Discussion:**

Household air pollution exposure is a major health risk that requires well-tested interventions. GRAPHS will provide important new evidence on the efficacy of both efficient biomass cookstoves and LPG, and will thus help inform health and energy policies in developing countries.

**Trial registration:**

The trial was registered with clinicaltrials.gov on 13 April 2011 with the identifier NCT01335490.

## Background

In recent years, global health advocates have come to see household air pollution (HAP) – exposure to air pollution in the home, primarily from cooking with solid fuels – as a prime target for interventions. According to one recent authoritative estimate, HAP accounts for 3.5 million avoidable deaths per year globally, and ranks fourth by disability-adjusted life years (DALYs) among modifiable risk factors [1]. Reliable evidence on the effectiveness of interventions is, however, sparse. Cleaner interventions cost more, and public health resources are scarce. In short, intervention planners need to know: *how clean is clean enough*? And, *what household energy technologies will get us there?*

The burden of disease from HAP arises when incomplete combustion of solid fuels (primarily wood, animal dung, and crop residue) in inefficient cookstoves emits substantial quantities of fine particles (specifically, particles less than 2.5 microns in diameter, or PM_2.5_), carbon monoxide (CO), and a host of other health-damaging pollutants [2]. Combustion may occur indoors, exposing all household members to high levels of air pollution, or it may occur outdoors, mostly exposing cooks and others who are near the fire. Regardless of the hearth location, average exposures are high [3, 4].

An extensive epidemiological literature links these exposures to adverse health outcomes. Systematic reviews and meta-analyses for child acute lower respiratory infections (ALRI) [5], chronic obstructive pulmonary disease [6, 7], lung cancer [6, 8], reduced birth weight [9], and cataract [6] all show evidence of an association with HAP. For cardiovascular disease, evidence for increased risk from biomass smoke exposure comes both from numerous observational studies [10] and from interpolating risks from tobacco smoke and ambient air pollution [11, 12]. Direct empirical evidence of causality is limited, however. Most studies have been observational and, therefore, vulnerable to uncontrolled confounding. In particular, solid fuel use correlates with poverty, and poverty is both difficult to measure and itself a driver of disease through myriad causal channels. Even the rare epidemiological studies that include plausible measures of poverty are prone to endogeneity that can arise from optimizing behavior by household decision-makers.

Few randomized trials linking cookstove interventions to health outcomes have been reported to date. In a pioneering study in Guatemala, Smith et al. reported significant associations between an intervention cookstove and severe pneumonia [13]. One other unpublished trial from India found that rudimentary mud stoves did not deliver expected sustained exposure reduction or health benefits [14]. As of late 2014, four additional trials were currently underway [15], but results were not yet available.

A number of studies have evaluated the effect of clean cookstove interventions on pollution concentrations or exposures [4]. While most have found statistically significant reductions in pollution, none have reported post-intervention concentrations that meet or exceed World Health Organization (WHO) air quality guidelines for PM_2.5_. Three factors push up post-intervention concentrations. Intervention cookstoves may not be particularly efficient, households may continue to use traditional cookstoves alongside the intervention stove, and emissions from sources outside the home may attenuate the benefits of the intervention.

The goal of the present paper is to describe the study design of the Ghana Randomized Air Pollution and Health Study (GRAPHS), a new study designed to provide experimental evidence both on the health effects of HAP and on the effectiveness of specific, policy-relevant clean cookstove interventions. GRAPHS is a cluster-randomized trial that tests the efficacy of both relatively low-cost efficient biomass cookstoves and liquefied petroleum gas (LPG). We deliver these interventions to pregnant women before their third trimester. Our study outcomes are birth weight and physician-assessed severe pneumonia incidence within the first year of life. Demonstration of these benefits could result in a governmental policy to include improved stoves as part of the standard prenatal care package for women of childbearing age in developing countries.

## Methods/Design

We hypothesize thatUse of clean cookstoves introduced before the third trimester of pregnancy will lead to a significant increase in average birth weight.Use of clean cookstoves starting before the third trimester of pregnancy will lead to a significant reduction in the risk of physician-assessed severe pneumonia within the first year of life.

We are testing these hypotheses in a cluster-randomized intervention trial involving 1225 maternal-infant pairs in the Kintampo North and South districts of Ghana, West Africa. Thirty-five rural communities were randomly assigned to one of two intervention arms, or to a control arm. Community-based fieldworkers identify pregnant women and enroll them into the study. Gestational age is determined via ultrasound (SonoSite Inc., Bothel, WA, USA) at the enrollment clinic visit [16].

In intervention communities, we distribute intervention cookstoves to pregnant women after enrollment, along with health insurance and an insecticide-treated bed net. The control group receives insurance and an insecticide-treated bed net at enrollment, and an efficient biomass cookstove at the completion of the postnatal follow-up period in the matched intervention communities. We assess real-time personal exposure to CO among all studied participants during pregnancy (four times each) and among the infants during the first year of life (three times each). We monitor subsets of mothers during pregnancy (once) and of the infants (once) for real-time and PM_2.5_ during one of the CO monitoring sessions.

We measure birth weight to the nearest gram using a Tanita BD 585 digital baby scale (Tokyo, Japan). We record the time elapsed between delivery and birth weight measurement, and only birth weights collected within 24 hours of delivery are considered valid. Birth length and head circumference are also measured, and a placental sample is collected for malaria assessment and archiving. Birth measures are obtained for both health facility and home births.

Fieldworkers check for respiratory symptoms at weekly intervals in the home for the first year of the child’s life. They assess symptomatic children for pneumonia using the Integrated Management of Childhood Illness guidelines [17]. Regardless of fieldworker assessment, the study refers all children with symptoms of respiratory infection or who are otherwise unwell to Kintampo Municipal Hospital for clinical evaluation by a study physician. The study provides transportation and assists with follow-up care as needed. The primary case definition for the outcome of severe pneumonia is physician-assessed history of cough or difficulty in breathing and tachypnea and lower chest in-drawing. Table 1 gives our full set of pneumonia outcomes.

**Table 1 Tab1:** Definitions of pneumonia outcomes

Classification	Signs and symptoms
Primary definition of physician-assessed severe pneumonia	History of cough or difficulty in breathing and tachypnea (fast breathing ≥ 60 breaths/minute in a child aged < 2 months
	≥50 breaths/minute in a child aged 2–11 months) and lower chest in-drawing
Secondary definition of physician- assessed severe Pneumonia 1	History of cough or difficulty in breathing and tachypnea (fast breathing ≥ 60 breaths/minute in a child aged < 2 months
	≥50 breaths/minute in a child aged 2–11 months) and lower chest in-drawing and chest X-ray consolidation or pleural effusion or other infiltrates as defined in a chest x-ray taken within 72 hours of admission
Secondary definition of physician- assessed severe Pneumonia 2	History of cough or difficulty in breathing and tachypnea (fast breathing ≥ 60 breaths/minute in a child aged < 2 months
	≥50 breaths/minute in a child aged 2–11 months) and lower chest in-drawing and an oxygen saturation less than 90 %
Tertiary definition of severe pneumonia assessed by community based fieldworkers	History of cough or difficulty in breathing and tachypnea (fast breathing ≥ 60 breaths/minute in a child aged < 2 months
	≥50 breaths/minute in a child aged 2–11 months)
Primary definition of pneumonia (physician-assessed)	History of cough or difficulty in breathing and tachypnea (fast breathing ≥ 60 breaths/minute in a child aged < 2 months
	≥50 breaths/minute in a child aged 2–11 months) and lower chest in-drawing
Secondary definition of Pneumonia 1	Primary definition and chest X-ray consolidation or pleural effusion or other infiltrates as defined in a chest x-ray taken within 72 hours of admission
Secondary definition of Pneumonia 2	Primary definition and an oxygen saturation less than 90 %

### Study setting

The research builds on an established collaboration between Columbia University in the City of New York and the Kintampo Health Research Center (KHRC) in Ghana. KHRC provides substantial surveillance and research infrastructure to support GRAPHS [18, 19]. In particular, GRAPHS draws heavily on the Kintampo Health and Demographic Surveillance System (KHDSS), which provides the opportunity to identify pregnant women and follow them up using the KHDSS address system [19].

The study area comprises rural communities in the forest-savannah transition zone in the middle part of Ghana. Households in the study region typically cook on traditional three- stone fires. Wood is by far the dominant fuel, though some households use charcoal as a secondary fuel [20]. Outdoor cooking is prevalent during the dry season, but nearly all households also have enclosed or covered kitchen areas for wet season cooking. In pilot studies leading up to the current work, we found 24 h average PM_2.5_ exposure to be approximately 130 μg/m^3^ [20]. Per the KHDSS database, prevalence of smoking is about 10 % in all households in the study area. Cigarette smoking is very rare among women, as most smokers are men. We assess cigarette use among study participants and other household members via questionnaire.

A cluster was defined as a community or group of communities that:Is located in Kintampo North or South Districts (the core study area for KHRC)Is primarily rural (in practice, this excluded the 2 district capital communities that are made up of approximately 40,000 people);

A woman is eligible to participate in the study if she:Is in the first or second trimester of pregnancy (gestational age ≤ 24 weeks; this is to ensure that the intervention is actually delivered and in use by 28 weeks)Is carrying a live singleton fetus (twins and higher order multiples are excluded)Is the primary cook in her household; andIs a non-smoker.

### Interventions

The trial includes a control arm and two intervention arms: an efficient biomass cookstove arm and a LPG arm. Fig. 1 depicts the intervention cookstoves, and Fig. 2 provides an overview of study procedures by arm.

**Fig. 1 Fig1:**
[figure not shown]
BioLite (left) and liquified petroleum gas (LPG) (right) cookstoves

**Fig. 2 Fig2:**
[figure not shown]
Flow chart

In the efficient biomass cookstove arm – hereafter called the “BioLite arm” – households receive two BioLite HomeStove cookstoves (BioLite Inc., Brooklyn, NY, USA). These stoves burn freely available biomass fuels, but do so in a constrained L-shaped combustion chamber that increases heat transfer efficiency relative to traditional three-stone fires (more energy to the pot per unit of wood). In addition, a fan blows air into the combustion chamber, which improves the combustion efficiency of the system. A thermoelectric generator powers the fan, enabling use without a connection to an electrical grid. While some versions of the BioLite provide power via a Universal S Bus (USB) port, we opted for a version that optimizes combustion efficiency at the expense of USB power.

Study participants in the LPG arm receive a two-burner LPG stove manufactured in Ghana by the Ghana Cylinder Manufacturing Co. (Accra, Ghana). We chose that particular stove because it is readily available in Ghana, both for the current study and for potential future distribution. Enrolled households also receive timely deliveries of LPG gas at no cost to the participants. GRAPHS leased a 5000-kg LPG tank to ensure continuous supply. If households run low on LPG prior to a scheduled delivery, they can contact their fieldworker and the study will make a special delivery. Control arm participants use their own three-stone traditional stoves for the duration of the trial and will receive one BioLite stove at the end of the study period. All participants receive an insecticide-treated net (ITN).

Community-based fieldworkers visit households every week to check up on the intervention stoves and address any problems. In the control areas the community-based fieldworker visits take place as in the intervention arms, and are framed as checkups on the ITNs.

### Power calculations

We performed power calculations based on a model for two-level cluster randomized trials. All calculations were performed using Optimal Design software (OD; [21]), and assume a binary treatment variable. We do not adjust for multiple comparisons because we conceptualize each comparison as testing a distinct hypothesis.

For the birth weight outcome, we calculated the intraclass correlation coefficient to be 0.07 from KHRC birth weight data [22], and used an effect size of 0.32 for the BioLite arm and 0.40 for the LPG arm (derived from [9, 23]). Based on these inputs we calculate a power of 0.84 for the LPG arm and 0.82 for the BioLite arm (with alpha = 0.05) for *n =* 455 for the BioLite and control arms and *n =* 315 for the LPG arm.

For the pneumonia outcome, our power calculations were hindered by the fact that we lacked prior data on acute lower respiratory illness (ALRI) incidence in Ghana. We used data generated by Enwere and colleagues in the Gambia, as part of a vaccine trial [24]. One advantage of the Gambia data is that it includes estimates for a pneumococcal conjugate vaccinated population, as exists in our study area. Physicians carried out all assessments in clinical settings, as will be the case in our study. We also draw on the exposure-response curve relating average PM_2.5_ exposures to relative risks (RR) for ALRI that was developed as part of the 2012 global burden of disease/comparative risk assessment [1, 12].

We define *P*(ALRI) as the probability that a child develop at least one episode of physician-assessed severe pneumonia during the year of surveillance. Multiple occurrences will be analyzed separately. The test statistic, which approximately follows the non-central *t* distribution, was calculated from the parameters in Table 2. The expression for the statistic is complex and is omitted here in the interest of brevity; see [21] for a full presentation (page 141). Using the inputs listed, we calculate that the power of the LPG arm to be 0.98 and the power of the BioLite arm to be 0.89 with an alpha of 0.05.

**Table 2 Tab2:** Inputs used for acute lower respiratory tract infection (ALRI) power calculation

Parameter	Value	Source	Comment
*P*(ALRI) for controls – all clinical ALRI	0.30	Enwere 2007 (Table 2, column 6, rows 1 and 2)	No ALRI incidence data is available for Ghana; the Enwere data, from Gambia, is the best available analogue. Per the CRA ER, the RR of this exposure level is 2.43
*P*(ALRI) for BioLite intervention arm	0.20	CRA ER curve	Assuming the CRA ER and an exposure reduction of 60 % (130 μg/m^3^ → 78 μg/m^3^), which gives an RR of 1.65
*P*(ALRI) for LPG intervention arm	0.15	CRA ER curve	Assuming the CRA ER and a residual exposure of 20 μg/m^3^, which gives an RR of 1.22
95 % plausible interval for *P*(ALRI) for controls	0.26 – 0.35	Enwere 2007	Estimated from Enwere et al. 2007
Level (α)	0.05	n/a	n/a

*CRA ER* comparative risk assessment exposure response, *LPG* liquefied petroleum gas, *P(ALRI)* probability of a child developing at least one episode of physician-assessed pneumonia during surveillance year, *RR* relative risk

Based on prior research projects undertaken by KHRC, we anticipate an attrition rate of approximately 15 %. Thus, to achieve our goal of *n =* 1225 study participants, we will enroll *n =* 1415. Frequent interactions and strong community support have kept attrition to a minimum to date.

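### Birth-weight power is stated without sidedness or clusters per arm: at the stated arm sizes BioLite reaches 0.82 only one-sided (about 0.71 two-sided), and then LPG should be about 0.89, not 0.84

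*Protocol article*

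**What the plan says.** All the birth-weight inputs are in the protocol article, Methods/Design.

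- Power calculations names a two-level cluster-randomized model run in Optimal Design software.
- Intraclass correlation: "we calculated the intraclass correlation coefficient to be 0.07 from KHRC birth weight data".
- Effects, read as standardized: the authors "used an effect size of 0.32 for the BioLite arm and 0.40 for the LPG arm".
- Arm sizes: "455 for the BioLite and control arms" and "315 for the LPG arm".
- Significance level: "with alpha = 0.05", with no mention of one or two sides.
- Result: "Based on these inputs we calculate a power of 0.84 for the LPG arm and 0.82 for the BioLite arm".

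The number of clusters comes from the opening of Methods/Design: "Thirty-five rural communities were randomly assigned to one of two intervention arms, or to a control arm", with 1225 maternal-infant pairs in total. The split of clusters by arm is not printed. The birth-weight hypothesis is directional (clean stoves "will lead to a significant increase in average birth weight"), but no one-sided test is declared anywhere in the article.

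**The concern.** The two powers are presented together as the output of one set of inputs, so one calculation should return both. On the ordinary two-sided reading of alpha 0.05, the BioLite figure looks too high by about 11 points. On a one-sided reading BioLite is right, but LPG looks too low by about 5 points at the stated arm sizes.

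Birth weight is one of the two main outcomes, and BioLite against control is one of its two comparisons with control. If the final test is two-sided, the chance of missing the assumed BioLite effect is about 29%, where the printed power implies 18%. Anyone weighing a null BioLite result by the printed power would give it more weight than the design supports.

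**Working it through.** **Inputs.** Intraclass correlation ρ = 0.07; effects d = 0.32 (BioLite) and 0.40 (LPG); alpha 0.05; n = 455, 455 and 315 for BioLite, control and LPG. These are from Power calculations. The 35 communities and 1225 pairs are from the opening of Methods/Design.

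**Clusters per arm (inferred).** 1225/35 = 35 pairs per cluster. Then 455/35 = 13, 455/35 = 13 and 315/35 = 9, and 13 + 13 + 9 = 35. Every stated number fits, but the split is an inference and assumes equal cluster sizes. The 1225 is the target after the anticipated 15% attrition, so no further reduction applies.

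**Formula.** With m pairs per cluster and J1, J2 clusters in the two arms:

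- SE = sqrt[(ρ + (1 − ρ)/m) × (1/J1 + 1/J2)]
- noncentrality λ = d/SE
- power from the noncentral t distribution with J1 + J2 − 2 degrees of freedom, or from the normal distribution as an approximation

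The common factor is 0.07 + 0.93/35 = 0.09657.

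**BioLite, 13 v 13.** SE = sqrt(0.09657 × 2/13) = 0.1219; λ = 0.32/0.1219 = 2.625; 24 df.

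**LPG, 9 v 13.** SE = sqrt[0.09657 × (1/9 + 1/13)] = 0.1348; λ = 0.40/0.1348 = 2.968; 20 df.

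| Test at 5% | BioLite (printed 0.82) | LPG (printed 0.84) |
|---|---|---|
| One-sided, t | 0.817 | 0.889 |
| One-sided, normal | 0.837 | 0.907 |
| Two-sided, t | 0.712 | 0.806 |
| Two-sided, normal | 0.747 | 0.843 |

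Each printed figure can be reproduced alone: BioLite 0.82 by the one-sided t-test, LPG 0.84 by the two-sided normal approximation. No row gives both.

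**Why the pair does not fit at the stated arm sizes.** The ratio of the two noncentralities is (0.40/0.32) × sqrt[(2/13)/(1/9 + 1/13)] = 1.13. The intraclass correlation and the cluster size cancel, so changing either leaves the ratio as it is. In the table LPG exceeds BioLite by 7 to 10 points. The printed gap is 2.

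**A route that gives both.** Take a one-sided t-test and treat LPG as balanced at its own size, 9 v 9 clusters (16 df). At ρ = 0.070 the pair is 0.817 and 0.833. At ρ = 0.068, which prints as 0.07, it is 0.824 and 0.840; at ρ = 0.069 it is 0.821 and 0.837. Both pairs round to 0.82 and 0.84.

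**Can a two-sided BioLite test reach 0.82?**

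- Pushing the rounding to ρ = 0.065 and d = 0.325: 0.747 (t), 0.781 (normal).
- Ignoring attrition, 1415/35 = 40.4 per cluster: 0.728 (t), 0.763 (normal).
- Required for 0.82 with the t-test, changing one input at a time: ρ of about 0.047, or d of about 0.365.

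**Detectable effects.** Two-sided t-test, 80% power, ρ = 0.07: about 0.36 SD for BioLite and 0.40 SD for LPG.

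**The case against.** The best defence is that the article never says two-sided. Its hypotheses are directional, and a one-sided 5% t-test on the stated inputs gives BioLite 0.817, which rounds to the printed value. A reader might infer that 0.82 cannot be obtained from its inputs. That is not supported: the article leaves sidedness open, and one permitted reading reproduces the figure.

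A reader might also infer that the two figures cannot come from any single convention. That fails too. A one-sided t-test with LPG taken as 9 v 9 clusters and an intraclass correlation of about 0.068 to 0.069 returns both. Setting aside the extra control clusters understates LPG power, so that simplification is conservative.

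Finally, the 13/13/9 split is not printed, so these results are conditional on it.

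These points limit the finding but do not remove it. The route that gives both figures needs a one-sided test that is declared nowhere, and a control group smaller than the 455 given in the same sentence as the powers. With 455 controls, one-sided LPG power is about 0.89. A directional hypothesis is not by itself a one-sided test, and alpha 0.05 without qualification is ordinarily read as two-sided. The split is the one that fits all the printed totals.

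**Conclusion.** The point holds as one of unstated basis and inconsistent reporting. Taken as a two-sided test, BioLite power is about 0.71 (0.75 by normal approximation) against 0.82 printed, and LPG is about 0.81 (0.84) against 0.84. Taken as one-sided, BioLite is right as printed and LPG should be about 0.89. At the stated arm sizes, none of the four conventions checked gives both printed values, so on any of them at least one figure is wrong or misleading as it stands.

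The conclusion assumes equal clusters of 35 split 13/13/9, an intraclass correlation of 0.07, and no covariate adjustment in the power model, since none is mentioned there. A reader might go on to infer that the trial must enrol more women. That does not follow: the shortfall exists only if the test is two-sided, and what needs correcting is the stated power.

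**What to change.** In Power calculations, state whether alpha 0.05 is one- or two-sided, give the clusters per arm, and report both birth-weight powers on that one basis with the stated arm sizes.

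- If two-sided: BioLite about 0.71 and LPG about 0.81 (noncentral t), with effects detectable at 80% power of about 0.36 SD and 0.40 SD.
- If one-sided: declare it, keep BioLite at 0.82 and correct LPG to about 0.89.
- If a different cluster split, intraclass correlation or covariate adjustment was used: state it and recompute both arms in the same way.

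The cost is a rewritten sentence and one or two changed numbers. Under a two-sided test the stated power becomes less favourable. Enrolment, conduct and analysis are unaffected.

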### Analysis plan

We plan to evaluate the impact of the interventions on birth weight and pneumonia using two methods. First, we will carry out intention-to-treat analyses for both birth weight (assessed as a continuous variable: grams at birth) and incidence of physician-assessed severe pneumonia (assessed as new cases per weeks of child observation). Second, we will carry out exposure-response analysis in which we pool data across arms and model how our outcome variables are related to exposure levels. We will use non-linear models that account for confounders and for clustering. Missing data will be imputed using standard multiple imputation techniques [30]. Both analyses will be carried out with and without adjustments for covariates. In particular, we will control for mother, household, and community characteristics. In the case of birth weight, we will also control for placental malaria.

In addition to these main analyses, we plan several subgroup analyses on our primary outcomes, including comparison of groups defined on residence type (compound versus freestanding households); proximity to main road; gestational age at recruitment; and density of other exposure sources. We also plan to carry out secondary analyses on other birth and health outcomes that we predict will respond to reduction in air pollution exposure.

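### The pneumonia power rests on a control risk of 0.30 labelled as all clinical ALRI, while the outcome tested is severe pneumonia; the protocol must say which event 0.30 describes

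*Protocol article*

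**What the plan says.** The protocol describes one quantity, P(ALRI), in three ways, all under Power calculations.

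- The text defines it "as the probability that a child develop at least one episode of physician-assessed severe pneumonia during the year of surveillance".
- The Table 2 row that supplies the value 0.30 is labelled "for controls – all clinical ALRI". It cites two rows of a table from a Gambian vaccine trial.
- The Table 2 footnote gives it as the "probability of a child developing at least one episode of physician-assessed pneumonia during surveillance year", without the word severe.

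The outcome itself is fixed in Methods/Design: "The primary case definition for the outcome of severe pneumonia is physician-assessed history of cough or difficulty in breathing and tachypnea and lower chest in-drawing".

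The arm risks of 0.20 (BioLite) and 0.15 (LPG) come from applying an exposure-response curve to the 0.30; the text describes that curve as giving relative risks for ALRI. With these inputs the protocol reports power of 0.89 for BioLite and 0.98 for LPG at alpha 0.05.

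**The concern.** In ordinary use, all clinical ALRI is a wider class than severe pneumonia with chest in-drawing. If 0.30 is the risk of the wider class, the control risk of the primary outcome is lower. At the same risk ratios there are then fewer events and less power. The protocol gives no severe-pneumonia risk, no severe fraction and no reason to treat the two risks as the same.

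Severe pneumonia is one of the trial's two hypotheses, and the results are meant to inform fuel and stove policy. A null result would be read against a stated power of 0.89 to 0.98, which the labelled inputs may not support. The BioLite comparison has the least margin.

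**Working it through.** **Inputs from the protocol.** Control, BioLite and LPG risks are 0.30, 0.20 and 0.15; the plausible interval for the control risk is 0.26 to 0.35; alpha is 0.05; the test statistic is a non-central t from a two-level cluster model. There are 35 communities and 1225 pairs, so 1225/35 = 35 per cluster. Arm sizes of 455, 455 and 315 (stated for birth weight) give 13 BioLite, 13 control and 9 LPG clusters.

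**Assumptions needed to reproduce the figures.** Equal cluster sizes, a two-sided test, and the interval 0.26–0.35 read as the 95 % spread of true risks between communities.

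**Formula (log-odds scale).**

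- τ² = [(logit 0.35 − logit 0.26)/(2 × 1.96)]² = [(−0.619 + 1.046)/3.92]² = 0.0119
- Variance = sum over the two arms of [τ² + 1/(35·p(1−p))]/J, where J is the number of clusters in the arm
- Non-centrality = (difference in logits)/√variance, with df = J₁ + J₂ − 2

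**Stated figures first.**

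- BioLite, 13 v 13: the logit difference is 0.539. Variance = (0.0119 + 0.1361)/13 + (0.0119 + 0.1786)/13 = 0.0260. Non-centrality = 3.34, df 24, power **0.893** (stated 0.89).
- LPG: power **0.992** with 13 v 9 clusters and **0.981** with 9 v 9 (stated 0.98).

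Both stated values are recovered, so they are the power at a control risk of 0.30.

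**Lower control risks.** The risk ratios (0.20/0.30 and 0.15/0.30), τ² and cluster numbers are held fixed. The control risks below 0.30 are assumptions, not figures from the documents.

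| Control risk | BioLite (13 v 13) | LPG (9 v 9 to 13 v 9) |
|---|---|---|
| 0.30 | 0.89 | 0.98–0.99 |
| 0.27 | 0.85 | 0.97–0.98 |
| 0.25 | 0.82 | 0.95–0.97 |
| 0.20 | 0.71 | 0.89–0.93 |
| 0.15 | 0.57 | 0.77–0.83 |
| 0.10 | 0.40 | 0.58–0.64 |

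Power of 0.80 is lost at a control risk of about 0.24 for BioLite, that is, at 0.24/0.30 = 80 % of the stated risk. For LPG it is lost at about 0.16 (9 v 9) or 0.14 (13 v 9).

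**Between-community spread.** On the risk scale, τ² = 0.0119 corresponds to an ICC of about 0.0119 × 0.30 × 0.70 = 0.0025. Table 2 says only that the interval was estimated from the Gambian source, not that it describes variation between communities. At a control risk of 0.30, an ICC of 0.01, 0.02 or 0.05 gives BioLite power of about 0.83–0.86, 0.75–0.80 or 0.55–0.63. The lower end of each range converts on the risk scale (τ² = ICC/0.21), the upper end on the latent logistic scale.

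**The case against.** The strongest reply is that the error may lie in the label. The text says plainly that P(ALRI) is severe pneumonia, and only one row label says otherwise. The source table is not at hand, and that trial's definition of clinical ALRI might itself have required chest in-drawing. If so, 0.30 is a severe-pneumonia risk, the row label is wrong, and the stated power stands for the at-least-one-episode outcome. This objection holds. A reader might infer that the severe risk must be below 0.30 and that the stated power is therefore wrong, but the documents do not establish this. They establish a contradiction that only the sponsor can settle.

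The footnote is also weak evidence for a broader event. Table 1 gives physician-assessed pneumonia the same criteria as physician-assessed severe pneumonia, including in-drawing, so in this protocol dropping the word severe need not change the event. That leaves the row label against the text.

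Two further inferences are tempting and unsupported. One is that BioLite power is close to a coin toss: that needs a control risk near 0.15 or below, and no severe fraction is given. At 0.27 the loss is only from 0.89 to 0.85. The other is that the birth weight ICC of 0.07 shows the pneumonia spread to be too small. That compares a continuous outcome with a binary one, and the result depends on the conversion scale. A sensitivity range is justified; a claim that the spread is wrong is not.

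The protocol also admits that it lacked Ghanaian incidence data. This explains the borrowed figure, but not the conflict over what it measures.

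**Conclusion.** The point holds as a contradiction about the input that drives the pneumonia power. As labelled, 0.89 and 0.98 are for a broader event than the primary outcome, and nothing in the protocol bridges the two. The arithmetic is sound.

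The size of any overstatement cannot be fixed from the documents. It runs from none, if 0.30 proves to be a severe-pneumonia risk, to BioLite power of 0.40 and LPG power of 0.58–0.64 at an assumed risk of 0.10. BioLite is the more exposed comparison. These values rest on equal clusters of 35, a two-sided test, unchanged risk ratios and the between-community spread implied by 0.26–0.35.

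One limit applies throughout. The Analysis plan assesses "incidence of physician-assessed severe pneumonia (assessed as new cases per weeks of child observation"), whereas the power is for a binary outcome. A rate analysis that counts repeat episodes could recover some power, so neither the stated nor the recomputed values are exactly those of the planned analysis.

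**What to change.** 1. State from the cited source which event 0.30 describes, and make the text definition, the Table 2 row label and the footnote agree.
2. Unless 0.30 is shown to be a severe-pneumonia risk, restate the primary-outcome power over a grid of control risks such as the one above, holding the risk ratios and the spread implied by 0.26–0.35 fixed. Give the cluster numbers used for each comparison.
3. Say whether 0.26–0.35 is a between-community spread, and add a sensitivity range for it, naming the ICC scale.

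Relabelling 0.89 and 0.98 as the power for all physician-assessed clinical pneumonia, and naming that a key secondary outcome, would not be a remedy. The protocol names no key secondary outcome, and Table 1 defines physician-assessed pneumonia identically to the primary outcome, so this would duplicate the endpoint or need a new definition.

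The work is a recalculation and some rewording. The only cost is a possibly less favourable stated power; no extra enrolment is needed, and the outcome and analysis do not change.
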